## Abstract

**Methods::**

This will be a multi-center, randomized, double-blind, placebo-parallel controlled trial. A total of 300 patients diagnosed with AMI and undergoing percutaneous coronary intervention within 12 hours of diagnosis will be randomized 1:1 into 2 groups: the control group that will be administered conventional Western medicine plus placebo and the trial group that will be administered XST along with the conventional Western medicine. The duration of treatment will be 3 months and the follow-up will be up to 6 months for both groups. The main efficacy indicator is the incidence of HF. The secondary efficacy indicators are cardiac function classification, 6-minute walk test score, TCM syndrome score, survival quality score, brain natriuretic peptide level, ultrasensitive C-reactive protein level, and cardiac ultrasound result. Data will be collected to analyze the underlying mechanisms by using IBM SPSS 23.0 software.

**Discussion::**

By investigating the efficacy and safety of CXSTC, this study will provide a clinical evidence base for the use of TCM in the prophylactic treatment of post-infarction HF.

## 1. Introduction

Post-infarction heart failure (HF) is when HF occurs after an acute heart attack (including ST-segment elevation myocardial infarct and non-ST-segment elevation myocardial infarct).^[1]^ Previously, a few China-HF studies showed that 11.2% of patients with HF had an obsolete heart attack.^[2,3]^ The Japanese Acute Heart Attack Registry Study found that among patients with ST-segment elevation myocardial infarction (MI) undergoing percutaneous coronary intervention (PCI), the readmission rate was higher among patients who developed HF than in those who did not experience HF within the first year.^[4]^ Numerous studies have shown a significantly higher risk of HF in patients after an acute heart attack than in patients who did not have a heart attack.^[5–8]^ The key to treating post-infarction HF mainly involves blocking the overactivation of the neuroendocrine system. Studies have shown that β-blockers and angiotensin-converting enzyme inhibitors (ACEIs) can improve survival in patients with MI but they require long-term treatment with the maximum tolerated doses.^[9]^ Owing to adverse effects such as electrolyte disturbances, renal insufficiency, and hypotension, patients find it challenging to tolerate drug therapy.^[10–14]^ Although the outcomes of patients with post-infarction HF have marginally improved with the development of pharmacological and non-pharmacological therapies, their all-cause mortality, cardiovascular event rates, and re-hospitalization rates remain high.^[15,16]^

Traditional Chinese medicine (TCM) has shown lower adverse effects in reducing HF symptoms and improving patients’ quality. As a common TCM for the treatment of angina pectoris in coronary heart disease, Compound Xueshuantong Capsule (CXSTC) has been clinically used for >20 years. Its main components include Xuan Shen (*Scrophularia ningpoensis*), Huang Qi (*Astragalus membranaceus*), San Qi (*Panax notoginseng*), and Dan Shen (*Salvia miltiorrhiza*), which are interrelated and form a complex and complementary whole.^[17]^ CXSTC has shown anti-thrombotic and myocardial protective effects in a rat model.^[18,19]^ Clinical studies have shown CXSTC can reduce the number of angina attacks,^[20]^ alleviate clinical symptoms,^[21–23]^ improve N-terminal pro-B-type natriuretic peptide levels and other efficacy indices,^[24]^ improve lipid metabolism,^[25,26]^ inhibit platelet activation, improve endothelial cell function,^[27]^ and reduce levels of serum ultrasensitive C-reactive protein and vascular endothelial growth factor after PCI in patients with coronary artery disease.^[28]^ Based on the above studies, we hypothesized that early intervention of acute MI (AMI) with CXSTC based on modern standardized medical therapy might be more effective in protecting the myocardium.

This trial will be conducted as a multi-center, randomized, double-blind, placebo-controlled clinical study, aiming to provide a clinical evidence-based basis for the prevention and treatment of post-infarction HF using TCM.

## 2. Methods

### 2.1. Study design

This will be a multi-center, randomized, double-blind, placebo-parallel controlled trial. Between January 2020 and December 2023 in 9 centers including The First Affiliated Hospital of Guangzhou University of Traditional Chinese Medicine, the Affiliated Hospital of Liaoning University of Traditional Chinese Medicine, Yueyang Integrated Hospital of Traditional Chinese and Western Medicine Affiliated to Shanghai University of Traditional Chinese Medicine, the First Affiliated Hospital of Guangxi University of Traditional Chinese Medicine, Hainan Hospital of Traditional Chinese Medicine, Maoming Hospital of Traditional Chinese Medicine, Dongguan People’s Hospital, the Second Affiliated Hospital of Guangzhou Medical University, and Beihai People’s Hospital, a total of 300 patients diagnosed with AMI and undergoing PCI within 12 hours of diagnosis, with the Chinese medicine diagnosis of “Qi-Yin deficiency and blood stasis,” will be randomly divided into 2 groups: the control group that will be administered conventional Western medicine plus placebo, and the experimental group that will be administered CXSTC along with the conventional Western medicine. Figure 1 shows a flow chart of the study. Figure 2 presents the schedule of enrollment, interventions, and assessments.

**Figure 1. F1:**
[figure not shown]
Flowchart of the study. CXSTC = Compound Xueshuantong Capsule.

**Figure 2 F2:**
[figure not shown]
. The schedule of enrollment, interventions, and assessments. NYHA = New York Heart Association.

### 2.2. Ethics and registration

This study will be conducted in accordance with the Ethical Principles for Medical Research from the Declaration of Helsinki and other relevant regulations. It has been approved by the Ethics Committee of the First Affiliated Hospital of Guangzhou University of Chinese Medicine and annual review (Ethics No. NO.ZYYECK [2019] 080). Before each patient is enrolled in this study, the investigator will provide a complete and comprehensive description of the purpose, procedures, and possible risks of this study to the patients or their representative and obtain written informed consent. Patients will be made aware of their right to withdraw from the study at any time, and the informed consent will be retained as a clinical study document for review. Patient privacy and data confidentiality will be protected during the study.

China Clinical Trials Registry registration number: ChiCTR1900026545.

### 2.3. Patients

#### 2.3.1. Diagnostic criteria for AMI.

(1) Definition and diagnosis of AMI

Refer to the 2015 Guideline on the diagnosis and therapy of ST-segment elevation MI and the 2016 Guideline on the diagnosis and therapy of non-ST segment elevation acute coronary syndrome.

(2) Killip classification

Refer to the 2015 Guideline on the diagnosis and therapy of ST-segment elevation MI.

#### 2.3.2. Diagnostic criteria for HF.

Refer to the Chinese guidelines for the diagnosis and treatment of HF 2018.

#### 2.3.3. Diagnostic criteria and efficacy evaluation of TCM.

Refer to the 2018 Guideline on the diagnosis and therapy of AMI by integrative medicine and the 2002 Guiding principles of clinical research on new drugs of Chinese medicines.

#### 2.3.4. Recruiting.

Patients diagnosed with AMI and undergoing PCI within 12 hours of diagnosis at each study center will be screened by the inclusion and exclusion criteria and then invited by the clinician after providing a complete and comprehensive description of the purpose, procedure, and possible risks of the study to the patient or their representative and obtaining written informed consent.

#### 2.3.5. Inclusion criteria.

(1) Compatible with the diagnosis of AMI.(2) Patients underwent PCI within 12 hours of infarction or PCI after emergency thrombolysis.(3) Patients with an ejection fraction of >50%.(4) Patients who meet the criteria of Chinese medicine identification of Qi and Yin deficiency and blood stasis.(5) Age between 18 and 75 years, regardless of sex.(6) Patients who voluntarily accept the corresponding treatment and sign the written informed consent.

#### 2.3.6. Exclusion criteria.

(1) Those with AMI Killip classification grade II or above.(2) AMI combined with serious complications such as cardiogenic shock (not corrected by conventional treatment) combined with mechanical complications.(3) Severe arrhythmias (such as rapid-type atrial fibrillation, ventricular tachycardia, and high atrioventricular block).(4) Those with a previous history of chronic HF or old MI.(5) Patients with combined cardiomyopathy, wind heart disease, severe heart valve disease, pericardial tamponade, hypertensive emergencies, pulmonary hypertension, severe chronic obstructive pulmonary disease or acute exacerbation of asthma, severe infections, etc.(6) Patients with severe primary diseases of the liver (alanine aminotransferase level ≥3 times the upper limit of normal value), kidney (creatinine ≥3 mg/dL or 265 μmol/L), endocrine system, and hematopoietic system, or psychiatric patients.(7) Patients with combined malignancies.(8) Patients who are allergic to multiple drugs and foods or with a known allergy to the ingredients of CXSTC.(9) Patients who cannot take care of themselves or cannot take oral medication.(10) Patients who have participated in other clinical studies within the previous 3 months.(11) Patients with a suggested or confirmed alcohol or drug abuse history.(12) Pregnant or lactating women.(13) Patients with a history of cerebrovascular accident and major surgery and trauma in the previous 6 months.

#### 2.3.7. Additional exclusion criteria.

(1) Patients who do not cooperate with randomization, do not take any trial drug after randomization, or use very little drug (<10%).(2) Patients who use the prohibited combinations of treatments or drugs, which would affect the effectiveness and safety determination.(3) No data after randomization.

The case will be judged for exclusion after a discussion between the principal investigator, data manager, statistical analysis expert, and sponsor during a blinded review.

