### 2.4. Sample size

Taking α = 0.05 and β = 0.15, a 2-sided test will be used. The estimated sample incidence of P_1_ = 25% for the test group and P_2_ = 43% for the control group will be brought into the following equation:

$$\begin{array}{l} n_{1}=n_{2}=1641.6\times {\left(\frac{u_{\alpha }+u_{2\beta }}{sin^{-1}\sqrt{P_{1}}-sin^{-1}\sqrt{P_{2}}}\right)}^{2} \end{array}$$

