### 2.6. Interventions

The basic treatment will involve following the guideline-guided drug regimen for post-PCI AMI and HF.

Refer to China Society of Cardiology of Chinese Medical Association 2015 Guideline on the diagnosis and therapy of ST-segment elevation MI, 2016 Guideline on the diagnosis and therapy of non-ST segment elevation acute coronary syndrome, and 2016 ESC Guidelines for the Diagnosis and Treatment of Acute and Chronic HF. Drug therapy will be selected based on the severity of the patient’s condition and indications. The indications, doses, and courses of treatment will be strictly formulated according to the guideline recommendations: Dual-anti platelet-therapy, statins, ACEI/angiotensin receptor blockers, β-blockers, anti-ischemic therapy drugs, etc. Those with acute HF after infarction will be treated according to the situation: diuretics, vasodilators, positive inotropic drugs, etc; those with stable acute HF or chronic HF with diuretics, ACEI/angiotensin receptor blockers, β-blockers, aldosterone receptor antagonists, anti-HF treatment drugs, etc.

Test group: basic treatment + CXSTC, 3 capsules/dose, 3 times a day with warm water.

Control group: Basic treatment + placebo, 3 capsules/time, 3 times a day, with warm water.

Duration of treatment: 3 months.

Follow-up: 6 months.

Combined medications: Except for the medications prescribed for the course of the study, the use of TCM (proprietary Chinese medicine, tonics, injections) will be prohibited for all patients; for drugs or other treatments that must be continued for preexisting comorbidities and their symptoms (other than the symptoms of the disease), the name, usage, dosage, and duration of the drug (or other treatment) shall be recorded in detail; in case of comorbidities or symptoms during the study period, all symptomatic treatments will be administered according to clinical routine, and the name, usage, dosage, and time of the drug (or other therapy) shall be recorded in detail; and combined medications and therapies that need to be used during the study in case of adverse events shall be recorded in detail in the case report form.

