### 2.7. Outcomes

#### 2.7.1. Efficacy indicators

(1) The main efficacy indicator will be the incidence of HF. The incidence of HF was recorded on days 3, 7, 14, 1 month, and 3 months after drug administration, and after discontinuation of the drug until 3 months.(2) Secondary efficacy indicators

① Cardiac function classification: before treatment and after drug administration on days 3, 7, 14, 1 month, and 3 months and after discontinuation of the drug until the 3rd month of the examination record.

② Cardiac ultrasound: the examination records shall be recorded before treatment and on days 7 and 3 months after drug administration.

③ Six-minute walk test score: recorded on days 7, 14, 1 month, and 3 months after drug administration.

④ TCM syndrome score: recorded before treatment and on days 7, 14, 1 month, and 3 months after drug administration. The efficacy = (the integral value before treatment − the integral value after treatment)/ the integral value before treatment × 100%); It is assessed at 4 levels: clinical recovery: clinical symptoms or syndrome score decreased by ≥95% from the baseline; marked efficacy: the syndrome score decreased by ≥70% and <95%; efficacy: the syndrome score was a decrease of at least 30% and <70%; invalid: the syndrome score was a decrease of <30%; and worsen: the syndrome score exceeded the baseline after treatment.

⑤ Quality of survival score (the Minnesota living with heart failure questionnaire): recorded before treatment and on days 14, 1 month, and 3 months after drug administration.

⑥ Brain natriuretic peptide level was recorded before treatment and on days 3, 7, 14, and 3 months after drug administration.

⑦ Ultrasensitive C-reactive protein level: recorded before treatment and on days 3, 7, 14, and 3 months after drug administration.

Total efficacy rate = (clinical recovery + marked efficacy + efficacy) cases/a total number of cases × 100%.

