### 2.9. Statistical analysis plan

All data will be statistically analyzed using SPSS 23.0 software. The measurement data will be expressed as mean ± standard deviation to test the normality of the samples. If the distribution is normal and the variances are homogeneous, the *t* test shall be used. The rank sum test will be used if the distribution is not normal or the variances are not equal. Count data will be expressed as percentages and tested by the χ^2^ test or Fisher method. Rank data will be tested by rank sum test; the Cox regression model will be used to observe the relationship between the risk of occurrence of endpoint events and each influencing factor. A 2-sided *P* value < .05 will be set as the significant level.

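### Section 2.3.7 excludes randomised patients for prohibited treatment or early stopping and does not confine this to a per-protocol set, so the primary HF comparison may lose the protection of randomisation

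*Protocol article*

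**What the plan says.** Section 2.3.7 follows the eligibility criteria but lists events that occur after randomisation. There are three grounds:

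- Patients who do not cooperate with randomisation, or who "do not take any trial drug after randomization, or use very little drug (<10" per cent of it).
- "Patients who use the prohibited combinations of treatments or drugs, which would affect the effectiveness and safety determination".
- "No data after randomization".

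On the procedure the section says: "The case will be judged for exclusion after a discussion between the principal investigator, data manager, statistical analysis expert, and sponsor during a blinded review".

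Section 2.6 supplies the prohibited treatment: "the use of TCM (proprietary Chinese medicine, tonics, injections) will be prohibited for all patients". It also sets treatment at 3 months and follow-up at 6 months.

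Section 2.7.1 states: "The main efficacy indicator will be the incidence of HF". HF is recorded on days 3, 7 and 14, at 1 and 3 months, and up to 3 months after the drug is stopped.

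Section 2.9 names tests but no analysis population. For the primary outcome the relevant sentence is: "Count data will be expressed as percentages and tested by the χ^2^ test or Fisher method".

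**The concern.** The randomised comparison is protected only while patients are analysed in the arm to which they were assigned. Section 2.3.7 is a written rule for removing some of them. It does not say that they leave only a per-protocol set, and no other section of the article keeps them in their assigned arm.

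Two grounds matter most, because they can remove patients whose HF status is already known:

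- **Prohibited treatment.** A patient who feels worse, or sees no benefit, has the most reason to turn to another Chinese medicine. This ground can therefore depend on the assigned capsule and on the course of the disease.
- **Early stopping with under 10% of the drug.** Intolerance or an early event can lead to this. The first two HF assessments fall inside the window.

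If either ground operates differently in the two arms, the HF rates compared at the end are those of selected groups. The test of the primary endpoint would then no longer have its stated 5% error rate.

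**Working it through.** **Step 1. What 10% of the drug means.** Section 2.6 gives a 3-month course at 3 capsules three times a day. Taking 3 months as 90 days, the course is 9 × 90 = 810 capsules. Ten per cent is 81 capsules, or 81/9 = 9 days. HF is recorded on days 3 and 7. A patient found to have HF at either visit who then stops the capsules meets the exclusion criterion after the primary event has been observed.

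**Step 2. Is there a sample-size reason to exclude?** Section 2.4 states: "Taking α = 0.05 and β = 0.15, a 2-sided test will be used", with HF rates of 25% (test) and 43% (control). Its arcsine formula, with 1.960 and 1.036 for the two normal deviates, gives 122.3, so 123 per arm and 246 in total. The stated total is 300. The difference may be an allowance left out of the article and is a separate matter. Power at 25% v 43% (pooled two-proportion test, two-sided 5%):

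| Analysed per arm | Share excluded | Power |
|---|---|---|
| 150 | 0% | 91.2% |
| 135 | 10% | 88.2% |
| 123 | 18% | 85.1% |

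So exclusions cost little power, and keeping everyone costs none. The issue is bias.

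**Step 3. How large could the bias be?** The documents give neither an exclusion rate nor an HF rate among excluded patients. Everything below is therefore assumed. With a true HF rate p in both arms (no drug effect), excluded share e and HF risk r among the excluded, the rate left in an arm is

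(p − e·r) / (1 − e).

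The type I error is the chance that a two-sided 5% test rejects when the analysed rates differ by that amount, with 150 × (1 − e) patients left per arm (normal approximation, pooled variance).

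| p | Excluded, test / control | HF risk in excluded, test / control | Analysed HF rate, test / control | Spurious difference | Type I error |
|---|---|---|---|---|---|
| 43% | 10% / 10% | 43% / 43% | 43.0% / 43.0% | 0 | 5.0% |
| 43% | 5% / 5% | 60% / 43% | 42.1% / 43.0% | 0.9 points | 5.3% |
| 34% | 10% / 10% | 60% / 34% | 31.1% / 34.0% | 2.9 points | 8.0% |
| 34% | 15% / 5% | 60% / 60% | 29.4% / 32.6% | 3.2 points | 8.8% |
| 43% | 10% / 10% | 80% / 43% | 38.9% / 43.0% | 4.1 points | 10.6% |
| 43% | 18% / 18% | 80% / 30% | 34.9% / 45.9% | 11.0 points | 42% |

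Here 34% is the mean of the two planning rates, (25 + 43)/2. Worked example for the fourth row: (0.34 − 0.15 × 0.60)/0.85 = 0.25/0.85 = 0.294 and (0.34 − 0.05 × 0.60)/0.95 = 0.31/0.95 = 0.326. The pooled standard error with 127.5 and 142.5 patients is 0.056, so the shift is 0.032/0.056 = 0.57 standard errors and the test rejects in 8.8% of trials.

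Every row with a difference has been set to favour the test arm. Swapping the arms gives the same size of bias against it.

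**The case against.** The strongest reply is that an article condenses a fuller plan. Analysis sets are usually defined in the analysis plan, and a blinded review attended by the data manager and statistician is just where cases are allotted to such sets. That has force. A reader might infer that no all-randomised analysis exists, but the article's silence does not show this. What stands is narrower: section 2.3.7 fixes an exclusion rule in writing and does not limit it.

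A reader might also infer that the rule hides adverse events by taking treated patients out of the safety data. The documents do not support this. The clause on effectiveness and safety explains why prohibited treatments matter and defines no safety population. Section 2.7.3 requires any adverse event to be recorded, and section 2.8 requires serious ones to be reported. The wording is ambiguous, and no more than that.

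Three further points are fair:

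- Dropping patients who took no drug or have no data is a common modified full-analysis-set rule. In a double-blind trial, never starting the drug is unlikely to depend on the assigned capsule.
- Most patients who stop will have passed about 9 days and stay in. Developing HF does not by itself trigger exclusion either, since section 2.6 allows HF drugs and bars other TCM.
- An exclusion imbalance of 15% v 5% is large for a blinded trial, and at the benign end there is no bias.

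Blinded review limits deliberate selection. It does not make the reasons for exclusion independent of treatment, and nothing in section 2.3.7 keeps the patient's HF status from those judging the case.

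**Conclusion.** The point holds in limited form. Followed as written, section 2.3.7 can remove randomised patients with observed HF outcomes for reasons that may depend on treatment or on worsening. Prohibited treatment and early stopping under 10% of the drug carry the point. The never-treated and no-data grounds are minor.

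The size is unknown. On the assumptions shown, type I error lies between 5% and about 11% in the moderate scenarios and reaches about 42% only in an extreme one (18% excluded per arm, HF risk 80% v 30% among them). The direction is not determined. The conclusion that section 2.3.7 needs rewording does not depend on which scenario is true: if an analysis plan does define an all-randomised set, the article's unrestricted rule should be brought into line with it.

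**What to change.** 1. State that the primary HF analysis includes all randomised patients in their assigned arm, whatever their drug intake or concomitant treatment, with a prespecified method for missing HF status.
2. Keep collecting the HF assessments already scheduled in section 2.7.1 from patients who stop the drug or use prohibited treatment.
3. Use the section 2.3.7 criteria only to define a supportive per-protocol set.
4. State that these criteria do not remove from the safety summary anyone who took at least one dose.

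The cost is mainly wording, since the HF visits are already planned. Non-adherence may dilute the effect estimate slightly. With all 300 patients kept, power at the planning rates is about 91%, above the 85% planned, which leaves some room for that dilution.
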